**8.2 Safety and Other Assessments**

Safety will be assessed by all SAEs that will be tracked monthly. SAEs will be managed by study investigators and/or subjects’ other medical practitioners per usual clinical practice.

Subjects will be asked about any injection site reactions at each visit. Vital signs (height, weight, blood pressure, pulse) and physical examination (general appearance, HEENT exam, cardiovascular exam, pulmonary exam, extremities, gross neurological status, cutaneous exam) will be assessed at each study visit.

**8.3 Adverse Events and Serious Adverse Events**

**8.3.1 Definition of Adverse Events**

An adverse event means any untoward medical occurrence associated with the use of an intervention in humans, whether or not considered intervention-related.

**8.3.2 Definition of Serious Adverse Event**

A Serious adverse event (SAE) is considered "serious" if, in the view of either the investigator or sponsor, it results in any of the following outcomes: death, a life-threatening adverse event, inpatient hospitalization or prolongation of existing hospitalization, a persistent or significant incapacity or substantial disruption of the ability to conduct normal life functions, or a congenital anomaly/birth defect.

Important medical events that may not result in death, be life-threatening, or require hospitalization may be considered serious when, based upon appropriate medical judgment, they may jeopardize the participant and may require medical or surgical intervention to prevent one of the outcomes listed in this definition.

**8.3.3 Classification of an Adverse Event**

**8.3.3.1 Severity of Event**

The following guidelines will be used to describe severity

• Mild – Events require minimal or no treatment and do not interfere with the participant’s daily activities.

• Moderate – Events result in a low level of inconvenience or concern with the therapeutic measures. Moderate events may cause some interference with functioning.

• Severe – Events interrupt a participant’s usual daily activity and may require systemic drug therapy or other treatment. Severe events are usually potentially life-threatening or incapacitating.

**8.3.3.2 Relationship to Study Intervention**

The investigator will assess the relationship between the AE and the study drug. All AEs will be classified as either related or not related to the study drug.

Related: The AE is known to occur with the study intervention, there is a reasonable possibility that the study intervention caused the AE, or there is a temporal relationship between the study intervention and event. Reasonable possibility means that there is evidence to suggest a causal relationship between the study intervention and the AE.

Not Related – There is not a reasonable possibility that the administration of the study intervention caused the event, there is no temporal relationship between the study intervention and event onset, or an alternate etiology has been established.

**8.3.3.3 Expectedness**

The study investigators will be responsible for determining whether an adverse event (AE) is expected or unexpected. An AE will be considered unexpected if the nature, severity, or frequency of the event is not consistent with the risk information previously described for the study intervention

**8.3.4 Time Period and Frequency for Event Assessment and Follow-Up**

The occurrence of an adverse event (AE) or serious adverse event (SAE) may come to the attention of study personnel during study visits and interviews of a study participant presenting for medical care, or upon review by a study monitor. All AEs including local and systemic reactions not meeting the criteria for SAEs will be captured on the appropriate case report form (CRF). Information to be collected includes event description, time of onset, clinician’s assessment of severity, relationship to study product (assessed only by those with the training and authority to make a diagnosis), and time of resolution/stabilization of the event. All AEs will be followed to adequate resolution. Any medical condition that is present at the time that the participant is screened will be considered as baseline and not reported as an AE. However, if the study participant’s condition deteriorates at any time during the study, it will be recorded as an AE. Changes in the severity of an AE will be documented to allow an assessment of the duration of the event at each level of severity to be performed.

All SAEs and AEs will start at the time of giving written informed consent for participation in the current study and finish with the end of study visit.

**8.3.5 Adverse Event Reporting**

At each clinical evaluation, the investigator or delegate will determine if any AEs have occurred. These will be recorded in a case report form. A medical diagnosis will be written if known. The investigator will follow the course of the AE.

**8.3.6 Serious Adverse Event Reporting**

The study clinician will immediately report to the sponsor any serious adverse event, whether or not considered study intervention related, including those listed in the protocol or investigator brochure and will include an assessment of whether there is a reasonable possibility that the study intervention caused the event. This report will occur within 24 hours of the investigator becoming aware of the event.

All serious adverse events (SAEs) will be followed until satisfactory resolution or until the site investigator deems the event to be chronic or the participant is stable.

**8.3.7 Reporting Events to Participants**

Subjects will be informed of adverse events if they are deemed related to the study drug and are unanticipated based on the study drug profile.

**8.3.8 Events of Special Interest**

Not applicable

**8.3.9 Reporting of Pregnancy**

Not applicable given the targeted study population

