**Study Population:**

*Sample size:*

From previous literature, we expect to evaluate 20-30 patients for secondary immunodeficiency to reach a goal of 10 patients to undergo treatment with subcutaneous immunotherapy.

*Gender:*

Both males and females will be enrolled in this study.

*Age:*

Eligible patients will be ages 18 and above.

*General health status:*

All patients with CLL who are medically stable with an expected survival of > 1 year per their primary hematologist/oncologist will be offered enrollment in this study.

*Geographic area:*

Patients will be recruited from hematology/oncology practices in Rochester, NY. The majority of patients will come from the CLL Registry and Rochester Regional Health, which includes over 300 patients. Other local hematology/oncology practices may also contribute patients to the study.

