**1.3 Schedule of Activities**

Please see below.

|  | Screening | | Therapy with Ig Replacement | | | | | | | | | Wash Out Period | | | |
| --- | --- | --- | --- | --- | --- | --- | --- | --- | --- | --- | --- | --- | --- | --- | --- |
| Study visit | V1 |  | V2 | V3 | V4 | V5 | V6 | V7 | V8 | V9 | V10 | V11 | V12 | V13 | V14 |
| Week of study |  |  | 1 | 2 | 3 | 4 | 8 | 12 | 16 | 20 | 24 | 28 | 32 | 36 | 40 |
| Consent | X |  |  |  |  |  |  |  |  |  |  |  |  |  |  |
| Urine pregnancy test* | X |  |  |  |  |  |  |  |  |  |  |  |  |  |  |
| Medical history |  |  | X | X | X | X | X | X | X | X | X | X | X | X | X |
| Vitals |  |  | X | X | X | X | X | X | X | X | X | X | X | X | X |
| Physical exam |  |  | X | X | X | X | X | X | X | X | X | X | X | X | X |
| QoL (SF 36 form) |  |  | X | X | X | X | X | X | X | X | X | X | X | X | X |
| Pt teaching for Ig |  |  | X | X | X |  |  |  |  |  |  |  |  |  |  |
| Dispense study Ig |  |  |  |  |  | X | X | X | X | X | X |  |  |  |  |
| Pneumovax (PPV23) | X |  |  |  |  |  |  |  |  |  |  |  |  | X |  |
| Tetanus/diphtheria | X |  |  |  |  |  |  |  |  |  |  |  |  | X |  |
| IgG | X | X |  |  |  | X |  | X |  |  | X |  |  | X | X |
| IgM | X | X |  |  |  | X |  | X |  |  | X |  |  | X | X |
| IgA | X | X |  |  |  | X |  | X |  |  | X |  |  | X | X |
| IgE | X | X |  |  |  | X |  | X |  |  | X |  |  | X | X |
| IgG for 23 serotypes of strep pneumo | X | X |  |  |  | X |  | X |  |  | X |  |  | X | X |
| IgG for diphtheria | X | X |  |  |  | X |  | X |  |  | X |  |  | X | X |
| IgG for tetanus | X | X |  |  |  | X |  | X |  |  | X |  |  | X | X |
| T and B cell panel | X |  |  |  |  |  |  |  |  |  |  |  |  | X |  |

* Will be completed in women of child bearing age

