**5. Study Population**

**5.1 Inclusion Criteria**

In order to participate in this study, a subject must meet all of the following criteria:

- Diagnosis of chronic lymphocytic leukemia
- Medically stable, with expected survival of > 1 year
- Able to understand and willingness to sign a written informed consent
- Able to comply with study procedures

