**5.2 Exclusion Criteria**

Any subject who meets any of the following criteria will be excluded from the study:

- Previously diagnosed primary immunodeficiency
- Additional immunosuppressive states as assessed by the primary or co-investigators
- Ongoing therapy with Ig replacement
- Serum IgG < 400 mg/dL

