**7. Study intervention discontinuation and participant discontinuation/withdrawal**

**7.1 Discontinuation of Study Intervention**

Study intervention will also halt if patients experience a hypersensitivity reaction to the study drug. The study intervention will also be halted if there is any serious adverse event deemed related to the study drug by the study investigators. If the study intervention is halted, then pre and post vaccination titers will be obtained after subcutaneous immunoglobulin has been discontinued for 3 months. Infections will continue to be tracked through patient contact, the electronic medical record, and pharmacy data. Quality of life data will still be tracked through patient contact.

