**7.2 Participant Discontinuation/Withdrawal from the Study**

The study intervention will be discontinued at any time a patient wishes to withdraw for any reason. Subjects will continue with medical care as prior to study enrollment.

All efforts will be made to continue to follow patients even if they are no longer receiving study drug. Study subjects may be withdrawn at any time based on the discretion of the investigator for safety, behavioral, or administrative reasons (including, but not limited to, an adverse event, lymphoma progression, protocol deviation, loss to follow up, non-adherence, or study termination).

In accordance with International Conference on Harmonisation (ICH) principles of Good Clinical Practice (GCP) the investigator always has the option to advise a subject to withdraw from the study over concerns of safety or subject well-being.

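### Section 8.3.9 sets pregnancy reporting aside because of the population, yet the protocol enrols women from age 18 and schedules a pregnancy test whose result no rule uses

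*Protocol*

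**What the plan says.** Section 8.3.9 of the protocol, on pregnancy reporting, reads in full: "Not applicable given the targeted study population".

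The other places that bear on it are these.

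- **Synopsis, Study Population.** "Both males and females will be enrolled in this study", and "Eligible patients will be ages 18 and above". No upper age limit is given.
- **Schedule of Activities (Section 1.3).** A urine pregnancy test is marked at V1 only, with the footnote "Will be completed in women of child bearing age".
- **Eligibility (Sections 5.1 and 5.2).** There are four inclusion and four exclusion criteria. None mentions pregnancy, contraception, menopause or the test result.
- **Screen failures (Section 5.4).** The protocol says there will be none. Section 4.1 offers therapy to every patient with an abnormal immune evaluation.
- **Stopping (Sections 7.1 and 7.2).** Study drug is halted for hypersensitivity or for a serious adverse event judged related to it. Patients may also stop at their own wish, and "Study subjects may be withdrawn at any time based on the discretion of the investigator for safety" or for other reasons in an open-ended list.

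**The concern.** The reason in Section 8.3.9 is valid only if no participant could become pregnant. The eligibility rules do not secure that, and the Schedule of Activities provides for such participants by testing them. One part of the protocol plans for women of child-bearing age and another treats them as absent.

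Two practical questions are left without an answer in the text. A site that obtains a positive V1 test is not told what to do with it. If a participant becomes pregnant during therapy or wash-out, a site that follows Section 8.3.9 as written has no duty under that section to tell the sponsor or to learn the outcome. What is at stake is participant safety and the completeness of safety data, not the statistical analysis.

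**Working it through.** The point is textual, so the check sets the provisions side by side. The only arithmetic is counting.

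**1. Does the population exclude pregnancy?** No. Sections 5.1 and 5.2 hold 4 + 4 = 8 criteria, and 0 of 8 limit child-bearing potential. With both sexes eligible from 18, the reason given in Section 8.3.9 does not follow from the protocol.

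**2. Is the test result used?** No rule in the shown text uses it.

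| Place where a result could act | Items | Items naming pregnancy or the test |
|---|---|---|
| Inclusion criteria, 5.1 | 4 | 0 |
| Exclusion criteria, 5.2 | 4 | 0 |
| Halting triggers, 7.1 | 2 | 0 |

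Read literally, a woman with a positive V1 test and an abnormal immune evaluation would still be offered therapy under Section 4.1.

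**3. When is the test done?** At 1 of 14 visits (V1). The other 14 − 1 = 13 visits have none: 9 on therapy (V2–V10) and 4 in wash-out (V11–V14). The Participant Duration entry in the synopsis gives 24 + 12 = 36 weeks for these two phases. The visit table numbers its weeks up to 40, a difference that does not affect this point.

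**4. What do the general safety rules already cover?**

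- Section 8.3.4 has recorded adverse events followed to resolution.
- Section 8.3.6 has serious events reported within 24 hours and followed until resolved, chronic or stable.
- Section 8.3.2 lists a birth defect among the outcomes that make an event serious, but pregnancy itself is not listed.
- Section 8.3.4 ends the collection of events at the end-of-study visit.
- Section 8.4.1 defines an unanticipated problem as one that is unexpected for the population and also suggests greater risk of harm. Section 8.4.2 sends such problems to the IRB and the sponsor.

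**5. What remains uncovered?** A complication that appears and is recorded during the study is followed. A pregnancy without a recorded complication is not reportable under any of these rules unless it also meets the greater-risk condition of Section 8.4.1. If it ends after the last visit, its outcome is not collected.

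**The case against.** The strongest reply is that Section 8.3.9 describes the patients the sponsor expects and the V1 test is a precaution for a rare exception. On that reading, existing rules would deal with the exception. Section 7.2 lets the investigator withdraw a pregnant participant for safety. History and physical examination at every visit from V2 to V14 give chances to detect a pregnancy. If pregnancy really lies outside the expected population, Section 8.4 may make it an unanticipated problem. Further, the protocol states no pregnancy risk of the product and refers its risks to a package insert that is not shown. The consent form is not shown either, and some administrative text was removed.

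Part of this stands. The discretionary withdrawal and the Section 8.4 route narrow the gap, so it would be too strong to say that a pregnancy could never reach the sponsor. The absence of repeat tests is not an error in itself, because the protocol sets no standard that requires them. The counts of rules and the missing action after a positive test apply to the shown text only.

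The conflict remains. Permission to withdraw a participant is not a duty to report or to follow an outcome. Section 8.4 applies only when greater risk is also suggested. An expectation about typical patients is not an eligibility rule, and the test row shows that the possibility was not dismissed. Wording in a consent form would not reconcile the schedule with Section 8.3.9.

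**Conclusion.** The concern holds. The reason given in Section 8.3.9 is contradicted by the synopsis, the eligibility criteria and the Schedule of Activities, and the V1 test result has no stated use.

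The severity is minor. The plan is to evaluate 20–30 patients and treat 10. The document does not say how many would be women of child-bearing age, and the number may be zero. The uncovered part is limited to the pregnancy itself and to an outcome first seen after the last visit. The primary objective and the descriptive analysis do not change. The conclusion uses no assumed figure. It assumes only that the eligibility, stopping and safety sections are complete as shown.

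**What to change.** Replace Section 8.3.9 with a rule of three parts: any pregnancy between consent and the end of study is reported to the sponsor; continuation of study drug is reviewed; and the outcome is followed past the last visit. Alongside this, state in Section 5.2 what a positive V1 test means for eligibility. Whether it excludes the patient is the sponsor's clinical decision.

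The alternative is to restrict Section 5 to patients not of child-bearing potential and delete the test row, which would make the present statement in Section 8.3.9 true.

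The first option costs a few sentences, since the test is already scheduled, plus one later contact for each pregnancy if any occurs. The second narrows eligibility slightly and saves the test.

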**8.4 Unanticipated Problems**

**8.4.1 Definition of Unanticipated Problems**

The Office for Human Research Protections (OHRP) considers unanticipated problems involving risks to participants or others to include, in general, any incident, experience, or outcome that meets all of the following criteria:

• Unexpected in terms of nature, severity, or frequency given (a) the research procedures that are described in the protocol-related documents, such as the Institutional Review Board (IRB)- approved research protocol and informed consent document; and (b) the characteristics of the participant population being studied

• Suggests that the research places participants or others at a greater risk of harm (including physical, psychological, economic, or social harm) than was previously known or recognized.

**8.4.2 Unanticipated Problem Reporting**

The investigator will report unanticipated problems to the reviewing Institutional Review Board (IRB). The UP report will include the following information:

• Protocol identifying information: protocol title and number, PI’s name, and the IRB project number

• A detailed description of the event, incident, experience, or outcome;

• An explanation of the basis for determining that the event, incident, experience, or outcome represents an UP

• A description of any changes to the protocol or other corrective actions that have been taken or are proposed in response to the UP.

UPs that are serious adverse events (SAEs) will be reported to the IRB and to the study sponsor within of the investigator becoming aware of the event. • Any other UP will be reported to the IRB and the study sponsor within of the investigator becoming aware of the problem.

**8.4.3 Reporting Unanticipated Problems to Participants**

The study investigators will report unanticipated problems to all study subjects.

**9. Statistical Considerations**

**9.1 Statistical Hypotheses**

Patients with CLL will demonstrate humoral immunodeficiency despite serum IgG ≥400 mg/dL

Secondary Hypotheses

- Subcutaneous Ig replacement therapy in increasing Ig levels
- Subcutaneous Ig replacement therapy will provide protective antibody titers for diphtheria, tetanus, and streptococcus pneumoniae
- Subcutaneous Ig replacement therapy will be safe and tolerable
- Quality of life (SF 36) will improve on subcutaneous Ig replacement therapy.

**9.2 Sample Size Determination**

There will be 10 subjects enrolled in this non-randomized, proof of concept study

**9.3 Populations for Analyses**

This will be a per protocol analysis dataset.

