**4.4 End of Study Definition**

A subject is considered to have completed the study if:

- They have a normal immune evaluation
- They have an abnormal immune evaluation and complete 6 months of therapy with subcutaneous Ig followed by the laboratory evaluation following a 3 month wash out period.

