**9.4 Statistical Analyses**

**9.4.1 General Approach**

Descriptive statistics will be used for each endpoint

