**9.4.4 Safety Analyses**

The safety analyses will be approached through descriptive statistics

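### Section 9.3 names per protocol as the only analysis set, with no exception for safety, so patients who stop for reactions would probably drop out of the tolerability result

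*Protocol*

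**What the plan says.** Protocol section 9.3 is a single sentence: "This will be a per protocol analysis dataset". It gives no membership rule. Section 9.4.1 adds that "Descriptive statistics will be used for each endpoint", and section 9.4.4 that "The safety analyses will be approached through descriptive statistics"; neither names another population.

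Safety is nevertheless something the study sets out to show. Section 9.1 lists as a secondary hypothesis "Subcutaneous Ig replacement therapy will be safe and tolerable", and section 8.1 places drug safety and tolerability among the efficacy assessments.

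On stopping, section 7.1 states "Study intervention will also halt if patients experience a hypersensitivity reaction to the study drug" and "The study intervention will also be halted if there is any serious adverse event deemed related to the study drug by the study investigators". It then provides for vaccine titres after three months off drug and for continued tracking of infections and quality of life. Section 7.2 allows withdrawal at the investigator's discretion, with adverse events and non-adherence among the reasons, and adds "All efforts will be made to continue to follow patients even if they are no longer receiving study drug". Section 8.3.4 collects adverse events from consent to the end-of-study visit.

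The closest thing to a completion rule is section 4.4. A treated patient has completed if "They have an abnormal immune evaluation and complete 6 months of therapy with subcutaneous Ig", followed by the laboratory evaluation after washout. A patient with a normal evaluation has completed on that evaluation alone, and section 5.4 keeps such patients in the study.

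**The concern.** A per-protocol set normally keeps patients who received treatment as planned. For safety this is the wrong condition, because stopping early for a reaction is itself the outcome of interest. If those patients leave the set, tolerability is described only in patients who tolerated the drug. Infections and quality of life are filtered the same way. The follow-up that section 7.1 plans after stopping would be collected and then left out of the analysis.

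The primary objective is affected less, but in a similar way. Whether a patient has humoral immunodeficiency is settled at the four-week evaluation. If membership of the set depends on later treatment, the diagnostic result comes to depend on drug tolerance and willingness to be treated, which have no bearing on it.

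**Working it through.** **Inputs.** From the protocol: 20–30 patients evaluated, 10 abnormal and treated, 10–20 normal (section 1.2); 10 subjects (section 9.2, no derivation given). Stopping counts and risks are assumptions.

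**The plan's own figures.** 20 − 10 = 10 and 30 − 10 = 20, so the 10–20 normal evaluations reproduce. There is no power calculation to check: the plan is descriptive and gives no alpha, power or effect size.

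**Tolerability.** Let k of 10 treated patients stop for a reaction. The all-treated set gives k/10. A set of section 4.4 completers gives 0/(10 − k), because each such patient is removed from numerator and denominator alike. Exact (Clopper-Pearson) 95% limits for x/n are the 0.025 quantile of Beta(x, n − x + 1) and the 0.975 quantile of Beta(x + 1, n − x). For x = 0 the lower limit is 0 and the upper limit is 1 − 0.025^(1/n).

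| k (assumed) | All treated | 95% CI | Completers | 95% CI |
|---|---|---|---|---|
| 1 | 1/10 = 10% | 0.3–44.5% | 0/9 = 0% | 0–33.6% |
| 2 | 2/10 = 20% | 2.5–55.6% | 0/8 = 0% | 0–36.9% |
| 3 | 3/10 = 30% | 6.7–65.2% | 0/7 = 0% | 0–41.0% |

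The completers column is zero whatever k is.

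**How likely this is to matter.** The chance that at least one of 10 patients stops for a reaction is 1 − (1 − p)^10. With assumed risk p:

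- p = 5%: 1 − 0.95^10 = 40%
- p = 10%: 1 − 0.90^10 = 65%
- p = 20%: 1 − 0.80^10 = 89%

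**Primary frequency.** Using every evaluated patient, the planned split gives 10/20 = 50.0% (27.2–72.8%) to 10/30 = 33.3% (17.3–52.8%). Under section 4.4 all normal patients are kept, but abnormal patients who decline therapy or stop it are not. If 2 of the 10 abnormal patients are lost (assumption):

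- (10 − 2)/(20 − 2) = 8/18 = 44%
- (10 − 2)/(30 − 2) = 8/28 = 29%

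The loss falls only on abnormal patients, so the frequency can only move down.

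**The case against.** The strongest reply is that the protocol never says early stoppers are excluded. Per protocol is undefined, section 4.4 defines study completion rather than an analysis set, and a patient halted under section 7.1 has followed the protocol. Membership rules are often left to a statistical analysis plan. All of this stands: exclusion is the likely reading, not a written rule. It does not remove the problem. The only set named is one that usually excludes these patients, nothing in section 9 exempts safety, and an all-treated safety set in a later plan would depart from section 9.3 as worded. Leaving the term open also allows membership to be settled after results are seen, in a study without blinding (section 6.3).

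It can also be said that the study is a small descriptive series, that no test or decision rule depends on the set, that the intervals above overlap widely, and that section 9.4.5 allows individual data to be shown. These points limit the consequence. But section 9.4.5 is only permissive, and a summary rate of zero by construction misdescribes tolerability at any sample size.

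A reader might go further and infer that patients with a normal evaluation have no place in the primary analysis, so that the result would be 10/10 = 100%. The documents do not support this. Section 4.4 counts these patients as completers and section 5.4 includes them. The 100% figure would need the set to be restricted to the 10 subjects of section 9.2, which section 9.3 does not do.

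Nor does section 7.2 guarantee particular data after stopping. It promises effort to follow patients; only section 7.1 lists what is collected.

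**Conclusion.** The concern holds in a limited form. Section 9.3 fixes a single, undefined per-protocol set and makes no exception for safety. On the usual meaning, or on the section 4.4 rule, the tolerability summary would show no stopping for reactions when the true count is 1, 2 or 3 of 10: a gap of 10 to 30 percentage points. The possible effect on the primary frequency is smaller, about 4 to 6 points downward if two abnormal patients are lost (33.3% to 28.6%, or 50.0% to 44.4%).

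These sizes rest on assumed counts and on reading per protocol as completers. If the set were defined to keep patients halted under section 7.1, the distortion from those halts would disappear. The safety part alone is reason to correct the wording before any data are analysed.

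**What to change.** Amend section 9.3 to name three sets:

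1. **Evaluated set**, for the primary frequency: all evaluated patients with serum IgG of at least 400 mg/dL, whether or not they were later treated or completed. Report how many lack paired pre- and post-vaccine titres.
2. **Treated set**, for safety, tolerability, infections and SF-36: everyone who received at least one infusion, using all available data, including data after stopping. Summarise Ig levels and titres in this set too, with the data available.
3. **Per-protocol set**, with its membership rule written out: supportive only, for Ig levels and titres.

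The cost is a few sentences. Sections 7.1 and 8.3.4 already plan most of the follow-up needed. There are two drawbacks. Reported tolerability may look less favourable. And section 7.1 does not say that the scheduled Ig draws continue after a halt, so Ig levels and on-schedule titres may be missing for some patients; the number with data should be shown at each visit.
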